|--------------------------------------------|----------------------------------------------------------------------------------------------------------------------------------------------------------------------------------------------------------------------------------------------------------------------------------------------------------------------------------------------------------------------------------------------------------------------------------------------------------------------------------------------------------------------------------------------|
| Radio-pharmaceutical administration | Subjects will receive an intravenous injection of 250 MBq ( $\pm 10\%$ ) of $^{18}\text{F}$ -FDG prior to surgery. LightPath® images should be taken approximately 145 minutes post-administration.                                                                                                                                                                                                                                                                                                                                          |
| Length of Study                     | Subjects included in the clinical study will be evaluated at screening and enrolled into the study. Data will be collected until the patient's surgical treatment is complete.                                                                                                                                                                                                                                                                                                                                                               |
| Primary Outcome Measure             | Agreement between margin status of WLE specimens as determined by intraoperative CLI + FAR LightPath® imaging and post-operative histopathology.                                                                                                                                                                                                                                                                                                                                                                                             |

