### 7.4. Inclusion Criteria

- Female subjects  $\geq 18$  years of age with a diagnosis of invasive breast cancer scheduled to undergo BCS
- Subjects who are able to give voluntary, written informed consent to participate in this study
- Subjects who are able to understand this study and are willing to complete all the study assessments

- Female subjects of childbearing age must have a negative pregnancy test (by Beta human chorionic gonadotrophin ( $\beta$ -HCG) qualitative analysis) or must have had a history of a surgical sterilisation or must give history of no menses in the past twelve months.

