## 7.5. Exclusion Criteria

- Subjects who have had surgery to the ipsilateral breast in the past 12 months
- Subjects who have had radiotherapy to the ipsilateral breast
- Subjects who have a known hypersensitivity to  $^{18}\text{F}$ -FDG
- Subjects who are pregnant or lactating
- Subjects who have an existing medical condition that would compromise their participation in the study.

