## **8.8. Study Duration**

### **8.8.1. Duration of Subject Participation**

The point of enrolment in the study is the point at which the subject provides written informed consent and participation in the treatment phase ends at the conclusion of surgery. Adverse events will be recorded until discharge, or for 24 hours after the first study procedure, whichever is sooner. Participants will return for a study completion visit at the time of the MDT decision whether to re-operate (1-2 weeks after completion of the initially planned surgery).

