### 11.7.2. Analysis of Secondary Outcome Measures

- Agreement between margin status of cavity shavings as determined by intraoperative CLI + FAR LightPath® imaging and post-operative histopathology will be assessed similarly to the primary outcome measure (section 11.7.1).
- Agreement between margin status of WLE specimens as determined by intraoperative CLI + FAR LightPath® imaging and routine intraoperative specimen x-ray will be assessed similarly to the primary outcome measure (section 11.7.1).

- Re-operation rate within the study cohort will be compared to the general breast cancer population undergoing a WLE at Guy's Hospital. The re-operation rate within Guy's Hospital is routinely recorded, audited and have remained consistent at 20 – 25% over many years.  
By recording the time required to intraoperatively image and assess each specimen, the average time added to the operating procedure can be determined.

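### The re-operation rate of a restricted cohort is set against an undefined general WLE audit figure of 20-25%, so the two rates cannot be shown to be comparable

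*Protocol*

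**What the plan says.** Section 11.7.2 of the protocol sets out the comparison: "Re-operation rate within the study cohort will be compared to the general breast cancer population undergoing a WLE" at Guy's Hospital. It adds that the site's rates are routinely recorded and audited and "have remained consistent at 20 – 25% over many years". Section 6.2 names the same comparator; the secondary outcome list in the synopsis (2.3) leaves out the hospital.

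Eligibility is narrower. Section 7.4 admits women "with a diagnosis of invasive breast cancer scheduled to undergo BCS". Section 7.5 excludes ipsilateral breast surgery in the past 12 months and "Subjects who have had radiotherapy to the ipsilateral breast".

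On timing, section 8.8.1 says: "Participants will return for a study completion visit at the time of the MDT decision whether to re-operate", 1-2 weeks after the initially planned surgery. The schedule of events (2.4) has nothing after that visit. For participants imaged late, section 11.6.1 summarises how often re-operation was decided on. The synopsis, under length of study, says: "Data will be collected until the patient's surgical treatment is complete".

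Section 11.7 calls most of the analysis descriptive, analyses secondary outcomes on both the ITT and the per protocol sets, and treats p-values from secondary endpoints as an aid to interpretation only.

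**The concern.** Fewer re-operations is the first potential patient benefit listed in section 3.2.3 and the unmet need that closes section 3.1. In a single-arm study, this external comparison is the only planned evidence on it. Such a comparison means something only if both rates describe similar patients, count the same event and run over the same time.

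The protocol secures none of the three. On its own wording the cohort is restricted and the comparator is general. The event is never defined on either side: a decision or a performed operation, breast only or axillary returns as well (axillary surgery is part of the trial, section 8.6.3), and within what period. The benchmark is a five-point range without numerator or denominator. A lower rate in the cohort could then be read as an effect of the imaging when it reflects who was enrolled or what was counted.

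**Working it through.** **Comparability, side by side**

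| Element | Study cohort | Comparator |
|---|---|---|
| Patients | Invasive cancer; no ipsilateral breast surgery in 12 months; no ipsilateral radiotherapy (7.4, 7.5) | General breast cancer population having WLE at the site (11.7.2); case mix not stated |
| Event | MDT decision at 1-2 weeks (8.8.1), or anything up to completion of surgery (2.3) | Re-operation, not defined |
| Window | 1-2 weeks, or open | Not stated |
| Period | Trial recruitment, about 24 months (8.8.2) | Many years, not specified |
| Rate | To be observed | 20-25% |

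The only re-operation rate in the protocol that carries a time window is the 20% within 3 months in section 3.1. It comes from a cited retrospective study, not from the site audit.

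**Inputs for the size of the benchmark problem**

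- Benchmark p0: 20% and 25% (11.7.2). This is an audit figure without derivation, so it cannot be recomputed.
- n: 60 enrolled and 54 analysed (11.6.2). With the 10% drop-out of section 11.8, 54/0.90 = 60, so these two figures agree.
- Level: two-sided 0.05, that is 0.025 in the lower tail. The protocol states it for the primary endpoint; applying it here is my assumption.

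**Step 1. Cut-offs.** Find the largest x with P(X ≤ x | n, p0) ≤ 0.025. This is the same as an exact 95% CI lying wholly below p0.

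| n | p0 | Largest x | P(X ≤ x) | P(X ≤ x+1) |
|---|---|---|---|---|
| 60 | 20% | 5 (8.3%) | 0.0121 | 0.0308 |
| 60 | 25% | 8 (13.3%) | 0.0212 | 0.0452 |
| 54 | 20% | 4 (7.4%) | 0.0101 | 0.0281 |
| 54 | 25% | 7 (13.0%) | 0.0241 | 0.0525 |

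So 6, 7 or 8 of 60, and 5, 6 or 7 of 54, lie below 25% but not below 20%. Exact 95% CIs at the edges of these zones: 6/60, 3.8-20.5%; 8/60, 5.9-24.6%; 5/54, 3.1-20.3%; 7/54, 5.4-24.9%.

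**Step 2. Chance of landing in that zone.** This is the power against 25% minus the power against 20%. The true rates are assumptions.

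| n | True rate | Power vs 20% | Power vs 25% | Difference |
|---|---|---|---|---|
| 60 | 10% | 0.437 | 0.858 | 0.421 |
| 60 | 12.5% | 0.223 | 0.667 | 0.444 |
| 54 | 10% | 0.361 | 0.832 | 0.471 |
| 54 | 12.5% | 0.179 | 0.639 | 0.460 |

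**Step 3. Error if the wrong end is used.** Suppose usual care is truly 20%, the imaging changes nothing, and 25% is the reference. The chance of a finding of a lower rate is P(X ≤ 8 | 60, 0.20) = 0.127, or P(X ≤ 7 | 54, 0.20) = 0.128, against a nominal 0.025.

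**The case against.** The strongest reply is that there is no verdict here to change. Section 11.7.2 names no test, level, margin or success rule, and section 11.7 judges diagnostic performance on the primary endpoint. A reader might infer from the arithmetic that the trial's conclusion turns on which end of the range is picked, or that it could be picked once the data are in. The protocol does not support that: the cut-offs above apply only if someone makes a fixed-rate comparison, and the method may be set in a statistical analysis plan, which was not available. This stands, and it limits the numerical part to a conditional statement.

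A reader might also infer that the two sides are known to differ, for instance that the audit counts operations performed while the study counts decisions. The protocol does not say what the audit counts, nor whether it includes pure DCIS. What can be said is that comparability is not shown; neither the direction nor the size of any bias can be derived. The contrast between a restricted cohort and a general population does rest on the protocol's own words.

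Finally, a last visit at 1-2 weeks and a later check of hospital records can coexist, so section 8.8.1 and the synopsis are not beyond reconciling. But no section says that such a check is made, and nothing is scheduled after the MDT visit.

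The comparator is already at the same hospital, and ITT analysis of secondary outcomes is already planned. Neither resolves case mix, event or window.

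**Conclusion.** The point holds as a weakness in how the comparison is fixed, not as proof of a biased result. As written, the study and audit rates cannot be shown to be comparable, and a difference between them could arise from case mix or counting alone. A purely descriptive comparison has the same weakness.

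The width of the benchmark adds a second problem, on two conditions: that a fixed-rate comparison is made, and that it uses an exact two-sided 0.05 criterion. Then 6-8 of 60 (5-7 of 54) re-operations give opposite readings at the two ends of the range. Such a count has a 42-47% chance of occurring if the true rate is 10-12.5%. Taking 25% when usual care is truly 20% raises the false finding of a lower rate to about 13%.

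The endpoint is secondary and the primary analysis is untouched. The change is still worth making before the data are seen, because a reduction in re-operations is the benefit readers will look for.

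**What to change.** - **Comparator.** Take it from the same hospital audit, restricted to invasive-cancer WLE patients who meet sections 7.4 and 7.5 as far as the audit records allow. State the calendar period, numerator and denominator.
- **Event.** Define one event and one window and apply them to both sides: for example, at least one further breast operation for margins, not counting axillary-only returns, taken from hospital records.
- **Follow-up.** Reconcile the synopsis (data until surgical treatment is complete) with section 8.8.1 (last visit at the MDT decision), and say whether records are checked after that visit. Name the same comparator population in sections 2.3, 6.2 and 11.7.2.
- **Reporting.** Give the cohort rate and the difference from the comparator, each with a 95% CI. Do not test against a point chosen from 20-25%.
- **Fallback.** If no matched extract can be had, show the cohort rate with its exact CI beside both 20% and 25%, and make no claim of reduction.

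The cost is one filtered audit extract, one record check per participant after the last visit, and a few lines of protocol text. No patients or visits are added. The matched comparator rate may turn out less favourable to the device than the quoted range.

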| Purpose             | 
This study is a prospective, single arm interventional study to evaluate the diagnostic accuracy of intraoperative Cerenkov luminescence imaging (CLI) plus flexible autoradiography (FAR) using the LightPath® Imaging System for intraoperative tumour margin assessment compared to post-operative standard-of-care histopathology in women undergoing breast-conserving surgery for breast cancer.
 
The intraoperative LightPath® images will be used to inform the operating surgeon about potentially detectable cancer at the margins of the excised specimen in an attempt to achieve better guided cancer surgery and complete tumour excision with clear resection margins. If a positive excision margin is detected on intraoperative LightPath® images, the operating surgeon will take a cavity shaving of the corresponding margin, provided more tissue can be taken.
 
Subsequent LightPath® imaging of the cavity shaving will inform the operating surgeon on the margin status of the shaving. If a positive excision margin is detected on intraoperative LightPath® images, the operating surgeon will take a further cavity shave of the corresponding margin, provided more tissue can be taken.
 
The resection margin status of the WLE specimen and cavity shavings (if any), as assessed by LightPath® CLI + FAR imaging will be compared with final histopathology results. A positive margin on histology will be defined as
 
 
• Invasive carcinoma: positive: <math>< 1\text{mm}</math>; negative <math>\geq 1\text{mm}</math>
 
• Ductal carcinoma in situ (DCIS) (if present): positive: <math>< 2\text{mm}</math>; negative <math>\geq 2\text{mm}</math>.
 
 |

|                                            |                                                                                                                                                                                                                                                                                                                                                                                                                                                                                                                                              |

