| Study Procedures   | 
Female participants with a diagnosis of invasive breast cancer scheduled to undergo breast-conserving surgery with or without sentinel lymph node biopsy (SLNB) or axillary lymph node dissection (ALND) will be screened and entered into the study if eligible.
 
All participants will receive an intravenous injection 250 MBq (<math>\pm 10\%</math>) of <math>^{18}\text{F}</math>-FDG prior to surgery. LightPath® images will be acquired within approximately 145 minutes following administration.
 
BCS will be performed as per standard of care, with the addition of intraoperative LightPath® CLI + FAR imaging.
 
Following resection, the WLE specimen and cavity shavings (if any), will be assessed using the LightPath® Imaging System. The intraoperative LightPath® CLI + FAR images will be used to inform the operating surgeon about potentially detectable cancer at or close to the excision margins of the excised specimen in an attempt to achieve better guided cancer surgery and complete tumour excision with clear resection margins. If a positive excision margin is detected on intraoperative LightPath® images, the operating surgeon will take a cavity shaving of the corresponding margin, provided more tissue can be taken.
 
Subsequent LightPath® imaging of the cavity shaving will inform the operating surgeon on the margin status of the shaving. If a positive excision margin is detected on intraoperative LightPath® CLI + FAR images, the operating
 |

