| Cavity shaving if indicated by LightPath® Imaging and/or specimen x-ray             |           | X              |           |                                                              |
| LightPath® imaging of cavity shaving, if applicable                                 |           | X              |           |                                                              |
| Histopathology analysis of WLE specimen and cavity shavings as per standard-of-care |           | X              |           |                                                              |
| Study related Adverse Events                                                        |           | X              | X         | X                                                            |
| Multidisciplinary team decision on re-operation ( within 1-2 weeks )         |           |                |           | X                                                            |

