### 6.2. Secondary outcome measures

- Agreement between margin status of cavity shavings as determined by intraoperative CLI + FAR LightPath® imaging and post-operative histopathology.
- Agreement between margin status of WLE specimens as determined by intraoperative CLI + FAR LightPath® imaging and routine intraoperative specimen x-ray.
- Re-operation rate within the study cohort compared to general breast cancer population undergoing a WLE at Guy's Hospital.
- Time added to operating procedure.

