### 8.6.2. BCS only

Participants scheduled to have BCS will be administered  $^{18}\text{F}$ -FDG intravenously in the Nuclear Medicine Department, approximately 145 minutes prior to CLI + FAR LightPath® imaging. BCS will be performed as per standard of care. Following resection, the WLE specimen and shavings (if any) will be examined intraoperatively using CLI + FAR LightPath® imaging. If the surgeons detect a positive signal, they will perform cavity shavings of the resection cavity area corresponding to the positive signal area. It will be at the surgeon's discretion to choose whether to act based upon the intraoperative LightPath® images.

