### 8.6.3. BCS plus axillary surgery (SLNB or ALND)

Participants scheduled to have BCS plus SLNB will receive  $^{99\text{m}}\text{Tc}$  and  $^{18}\text{F}$ -FDG.  $^{99\text{m}}\text{Tc}$  will be injected in the peri-areolar region and  $^{18}\text{F}$ -FDG administered intravenously in the Nuclear Medicine Department, approximately 145 minutes prior to CLI + FAR LightPath® imaging. Blue dye might be injected intraoperatively according to the local protocol; BCS and axillary surgery will be performed as per standard of care. In patients undergoing an SLNB, a collimator attached to the gamma-probe will allow directional detection of lymph nodes and shield the probe from  $^{18}\text{F}$ -FDG activity from the main tumour. Imaging procedures of the WLE specimen will be as described in section 8.6.2.

Sutures and surgical clips will be placed on the WLE specimen to record the anatomical orientation, as per standard practice. Based on the information on the LightPath® images additional sutures may be used to allow precise mapping between the histopathological analysis and CLI + FAR LightPath® imaging. Information on the surgical procedure will be recorded on the study case report form (CRF).

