### 11.6. Data Analysis

#### 11.6.1. Analysed Population

All participants enrolled into the study will be assigned to the following analysis sets:

- The intention to treat (ITT) analysis set. This will comprise all patients assigned to treatment.
- The Per Protocol analysis set. This set will comprise all participants who complete the study according to the protocol and who were compliant with assessment procedures (i.e., completed follow-up visits in accordance with local practice). It includes only those participants whose WLE specimens, and cavity shavings (if any) specimens were imaged within the time-window of approximately 145 minutes post-injection.

Further sensitivity analysis and summaries will be conducted based on sub-sets of the per protocol analysis set: e.g., subsets based on breast cancer diagnosis prior to surgery (invasive/DCIS), age etc.

A summary of the rate of decision to re-operate in the “Delayed LightPath® image set” (any participant for whom LightPath® Image of WLE and any cavity shaving specimens is outside the optimal time-window) will be presented as these participants will be excluded from the per protocol analysis set.

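### Time added to the operation is measured by imaging and assessment time alone, so the time to excise LightPath-directed cavity shavings is not counted (minor)

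*Protocol*

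**What the plan says.** Section 6.2 and the Synopsis list "Time added to operating procedure" as the last secondary outcome. This is a property of the whole operation. Section 11.7.2 gives the only account of how it is obtained: "By recording the time required to intraoperatively image and assess each specimen, the average time added to the operating procedure can be determined".

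The workflow contains more than imaging and reading. In the Synopsis, after a positive image of the wide local excision (WLE) specimen, "the operating surgeon will take a cavity shaving of the corresponding margin, provided more tissue can be taken". That shaving is imaged in turn and, if it is positive, "the operating surgeon will take a further cavity shave of the corresponding margin, provided more tissue can be taken". Section 8.6.2 says that "the WLE specimen and shavings (if any) will be examined intraoperatively", and section 11.6.1 refers to "any cavity shaving specimens", so an imaged shaving counts as a specimen.

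Sections 7.2.2 and 10.3 acknowledge that LightPath may bring shavings beyond those of usual surgery. The Schedule of Events shows that a shaving can have more than one trigger: "Cavity shaving if indicated by LightPath® Imaging and/or specimen x-ray". The protocol plans no comparison of total operating time with a control group or with past operations.

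**The concern.** Section 11.7.2 treats two quantities as the same: the time to image and read specimens, and the time by which the operation is lengthened. They differ whenever LightPath leads the surgeon to remove tissue that would otherwise have stayed. That step takes operating time and is caused by the device, but it is outside what is timed.

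The omission falls entirely on women with a positive image who then have a directed shaving, and these are the women in whom the device changes the operation. Section 3.1 lists longer surgery among several reasons why earlier margin techniques did not become standard, so readers will look at this figure. The study has a single arm and no total-time comparison, so this definition carries the whole outcome. If clock times for directed shavings are not recorded during surgery, no later analysis can recover them.

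**Working it through.** The protocol states no figure for added time, so there is nothing to reproduce. The check sets the timed steps against the steps that LightPath adds, then sizes the gap.

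**Steps added by LightPath and whether section 11.7.2 times them**

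| Step | Timed? |
|---|---|
| Imaging and reading the WLE specimen | Yes |
| Excising a shaving because the image is positive | No |
| Imaging and reading that shaving | Yes, it is a specimen |
| Excising a further shaving because the first is positive | No |
| Imaging and reading the further shaving, if done | Yes |

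Only the excision steps are missing.

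**How many women could be affected**

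Inputs from section 11.6.2: prevalence of positive margins 0.20, sensitivity 0.95, specificity 0.90.

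P(positive image) = prevalence × sensitivity + (1 − prevalence) × (1 − specificity) = 0.20 × 0.95 + 0.80 × 0.10 = 0.19 + 0.08 = 0.27.

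That is 0.27 × 54 = 14.6, about 15 of the 54 analysed women, or 0.27 × 60 = 16.2, about 16 of the 60 enrolled. These women are candidates for a directed shaving. The number who have one may be smaller, because sections 8.6.2 and 8.6.4 leave the response to the surgeon and the Synopsis requires that more tissue can be taken.

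**How many minutes are missed**

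The documents give no durations. Assume i minutes to image and read a specimen and s minutes to excise a shaving, with one shaving for each woman with a positive image and no overlap with other surgery.

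- Recorded per operation, if summed: i × (1 + 0.27).
- Added per operation: i × (1 + 0.27) + 0.27 × s.
- Shortfall: 0.27 × s on average over all operations, and s in a woman with a directed shaving.

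| Assumed i | Assumed s | Recorded mean (min) | Added mean (min) | Shortfall, all women (min) | Shortfall, woman with a shaving (min) |
|---|---|---|---|---|---|
| 10 | 3 | 12.7 | 13.5 | 0.8 | 3 |
| 10 | 5 | 12.7 | 14.05 | 1.35 | 5 |
| 10 | 10 | 12.7 | 15.4 | 2.7 | 10 |

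The shortfall in minutes does not depend on i. With i = 10, a woman with one directed shaving has 2 × 10 = 20 minutes recorded against 23 to 30 added, so 3/23 = 13% to 10/30 = 33% is missed. A second directed shaving adds a further s minutes to the shortfall.

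**The case against.** The strongest reply is that timing the device step alone is a reasonable scope. Some shavings would be taken on specimen x-ray anyway, so not all shaving time belongs to LightPath. Section 10.3 calls the extra shavings a minor addition, although it is speaking of risk. The missed time is small on average, and section 11.7 rests the evaluation of LightPath on the primary endpoint. All of this stands as to size, and it explains why directed and x-ray-led shavings must be recorded apart. It does not rescue the wording: a measure of the device step should not be reported as the lengthening of the operation.

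A reader might infer three stronger points that the protocol does not support.

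- *Repeat cycles are left out.* They are not. Shavings are imaged and count as specimens, so their imaging and reading time is recorded.
- *The result is a mean per specimen.* With one imaged shaving for each positive woman there would be 1.27 specimens per operation, and such a mean would understate imaging time per operation by 1 − 1/1.27 = 21%. But section 11.7.2 speaks of the average time added to the procedure, which fits summing within an operation at least as well. The unstated summing step is a detail that an analysis plan can settle.
- *Imaging during axillary surgery is wrongly counted as added.* This is possible. Section 8.6.3, however, says only that "BCS and axillary surgery will be performed as per standard of care", with nothing on whether imaging runs at the same time, and section 8.6.4 has the operating surgeon read the images.

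**Conclusion.** The point holds in a limited form. The rule in section 11.7.2 does not yield the outcome named in section 6.2, because it leaves out the time to excise shavings taken on account of LightPath. That part needs no assumption, since it follows from the protocol's own description of the procedure.

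On the planning values, about 27% of women are candidates for such shavings, as an expectation before surgeon discretion and tissue limits. The size in minutes rests on assumed durations: 3 to 10 minutes per directed shaving gives 0.8 to 2.7 minutes on average over all operations with one shaving per positive woman.

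The missing excision time biases the figure downwards. If imaging does overlap with axillary surgery, the net error could go the other way, but nothing in the protocol shows that it does.

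Severity is minor. The outcome is secondary and descriptive, with no hypothesis or threshold attached, and neither the sample size nor the primary analysis is affected.

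**What to change.** Reword the last sentence of section 11.7.2 so that the outcome is defined per operation:

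- Sum imaging and assessment time over all specimens in the operation.
- Add the excision time of shavings taken because of a LightPath image, with the indication for each shaving recorded as LightPath, x-ray or both, so that x-ray-led shavings are kept apart.
- Note any interval in which other planned surgery was proceeding, and do not count it as added.
- Average the per-operation totals over operations.

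The case report form needs start and stop clock times for imaging, reading and each shaving, a field for the indication, and a field for concurrent surgery. These have to be in place while operations are being done.

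If the extra fields are not wanted, keep the present measurement and rename the outcome *imaging and assessment time* in the Synopsis and in sections 6.2 and 11.7.2.

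The cost of the first option is a few form fields, one reworded sentence and a figure that may look less favourable. The second costs only the wording, but gives up the claim to report added operating time. Neither changes how patients are treated.
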